## Methods

### Sample size, inclusion & exclusion criteria

Sample Size is determined by two means; literature has worked with sample sizes averages between 10–40 participants, due to the long training period and evaluation requirements [30,31]. Sample size was calculated determining F-tests family for ANOVA repeated measures between and within interactions, given a moderate effect size of 0.25, alpha error prob of 0.05 and power of 0.80, two groups and two measurements. Effect size was determined with related previous works, where effect sizes of behavioral auditory discrimination measurements are reported from moderate to large, based on Cohen’s d and Cohen’s f calculations [32–35]. Larger effects sizes have been suggested when individuals were submitted for first time to auditory devices [36].

G*Power 3.1 points a total sample size for both groups of 34. Considering two independent groups for auditory discrimination training (ADT) implementation, sample size for Group A (control), and Group B (experimental) will be equally distributed.

A total of 40 participants will be recruited and enrolled in the study, as described in Fig 1, predicting a sample rejection of ~10%. Each of them will be randomly assigned to one of two groups (control group or experimental group) depending on the training methodology they will receive. Sample size for each group (non-game-based ADT and game-based ADT) is 20 individuals each. Assignments of each participant will be randomized using simple randomization 1:1 allocation ratio to select the group for the training methodology, avoiding bias on trials.

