### Expected outcomes & analysis

The primary outcome measures are related to neuro audiological changes in auditory processing. AEPs to be obtained are Mismatch Negativity and P3 components (continuous). Additionally, number of discrimination trials (discrete) will be registered. The secondary outcome measures are the in-game indicators such as time in each activity (continuous), accuracy (discrete) and attempts (discrete) to relate directly changes in audiological measures and game performance. The expected outcome of ADPQ is to increase the average score, that indicates a better perceived state and performance in auditory discrimination tasks that would be correlated with the in-game indicators and the electrophysiological measurements. The expected comparison outcome for AEP, it is expected an increase in evoked potentials amplitude and a decrease in latencies. For the in-game indicators it is expected to increase accuracy answers and decrease tasks’ solving time.

Once obtained and processed KPIs and discrimination threshold results, data will be analyzed with the following tools. Each of them will compare before and after auditory training KPIs and AEPs tests.

A 2-way analysis of variance (ANOVA) with repeated measures will be done considering the following factors.

For pre & post training measurements to determine individual performance of each methodology and contrast the improvement of each (within factors).For training group. Both methodologies have a similar distribution of activities to accomplish withing the training. Each group will be evaluated to determine if some activity yielded to a more significant difference in the overall performance (between factors).Finally, and mainly, for AT methodology groups to analyze and compare the final performance between the game-based experimental groups and the non-game-based control group and conclude if there is a significant difference between them.

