The following cases are proposed to test main 2-way ANOVA with repeated measures assumptions (normality, sphericity and equal variance) [37,38]. Normal distribution will be addressed using a histogram and Shapiro-Wilk test. If no normal distribution is found, data transformation (log or sqrt) will be conducted to repeat the normality test. Treating Type I errors of heteroscedasticity, sphericity would be addressed through a Maulchy’s test. If no sphericity was found, Greenhouse-Geisser correction would be conducted to adjust degrees of freedom and repeat sphericity test. Since this study within-subjects factor (repeated measures) is only having two measurements, sphericity assumption is not required due to no covariance comparisons. If normal distribution is not corrected, repeated measures ANOVA non-parametric equivalent test will be used (Friedman’s test). An additional Barlett’s test would be done for equal variance assumption if ANOVA normality is confirmed. If equal variance is violated, robust ANOVA may be considered.

Bonferroni post-hoc test will be conducted, using multiple t-tests times p-values (to avoid increase in alpha error). Analysis software to be used is Minitab with a level of significance of 0.05.

Possible spillover effects that could bias primary outcome measures are related to 3 main conditions:

Participants discrimination performance: This effect is considered through a discrimination performance questionnaire that the participant answer to address biases during tests of outcome measures.Participants health condition (auditory pathways related): This effect is addressed through rescheduling the tests when hearing health condition is better.Participants simultaneous training: This effect is addressed in the inclusion criteria where no additional formal auditory training is performed by the participant at the time of intervention.

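### Friedman's test, the fallback for data that stay non-normal after transformation, has no arm term, so any outcome reaching it loses the game versus non-game comparison

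*Protocol article*

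**What the plan says.** Under Expected outcomes & analysis, the Protocol article plans a two-way ANOVA with repeated measures. Time (pre, post) is the within factor and training group the between factor. The comparison of game-based with non-game-based training is described as the main purpose. The primary measures are electrophysiological: "AEPs to be obtained are Mismatch Negativity and P3 components (continuous").

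The same section sets a chain of rules for non-normal data. Normality is examined by histogram and Shapiro-Wilk test. If it fails, "data transformation (log or sqrt) will be conducted to repeat the normality test". If it is still not achieved, "repeated measures ANOVA non-parametric equivalent test will be used", with Friedman's test given in brackets. Robust ANOVA is mentioned only for unequal variances, and that check is made only once normality is confirmed. The post-hoc tests are Bonferroni-adjusted t-tests. No rank-based or permutation test of arm, or of arm by time, is named.

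The section Sample size, inclusion & exclusion criteria sizes the trial by the "F-tests family for ANOVA repeated measures between and within interactions". Its inputs are f = 0.25, alpha 0.05 and power 0.80, for two arms each measured twice. The result "points a total sample size for both groups of 34". Forty are to be enrolled in two independent groups by "simple randomization 1:1 allocation ratio".

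**The concern.** Friedman's test ranks the repeated measurements inside each participant and asks whether the ranks differ systematically between occasions. It is the rank counterpart of a one-factor within-subject ANOVA. It has no place for a between-subject factor, so it is not the counterpart of a group by time ANOVA. The participants in the two arms are different people and are not matched, so arm cannot be made the within-block factor either. Running the test separately in each arm gives two pre-post statements and still no comparison of the arms.

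At stake is the trial's main question on each outcome that takes this branch. Both arms receive active training and the article expects improvement. A significant Friedman result is therefore likely even when the two methods are equally good, and it could be reported as if it answered the question about the methods.

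**Working it through.** **Inputs from the article.** f = 0.25, alpha 0.05, power 0.80, k = 2 groups, m = 2 measurements, stated N = 34, enrolled 40, anticipated loss about 10%.

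**Inputs assumed.** The pre-post correlation rho is not stated; 0.5 is used. The number analysed per arm is taken as 18 (40 less 10% is 36), with 17 and 20 as the range.

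**1. The plan's own figure.** For the within-between interaction, lambda = f² × N × m / (1 − rho), with 1 and N − 2 degrees of freedom. At N = 34, lambda = 0.0625 × 34 × 2 / 0.5 = 8.5 on (1, 32) df, and power is 0.807. N = 34 is the smallest even total reaching 0.80, so the stated figure reproduces. Power at N = 40 is 0.869. With rho = 0.3 the required N would be 46, and with rho = 0.7 it would be 22. The trial is thus sized for a test of arm by time.

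**2. What that effect means on the change scale.** With SD 1 at each time and rho = 0.5, the SD of change is √(2 × (1 − 0.5)) = 1. A two-sample comparison of change has squared non-centrality δ² × N / 4. Setting this to 8.5 at N = 34 gives δ = 1. The planned effect is a between-arm difference in change of 1 SD of change.

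**3. Friedman's test with two measurements.** Let b be the number of participants who increase, out of N. The statistic is Q = (2b − N)² / N on 1 df. Arm does not appear in it, and exchanging the arm labels leaves Q unchanged.

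**4. Equal gains, no arm difference.** At N = 36, Q exceeds 3.84 when |2b − 36| > √(36 × 3.84) = 11.8, that is, when b ≥ 24 or b ≤ 12. If both arms gain 0.8 SD of change, each participant increases with probability Φ(0.8) = 0.788. The binomial probability of rejection is then 0.971. Simulation agrees at 97%, and gives 96-97% at 17 and 20 per arm. Mann-Whitney on change rejects in about 5%.

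**5. The planned 1 SD difference, placed in different ways.** Normal changes, 17-20 per arm:

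| Change in the two arms (SD) | Friedman rejects | Mann-Whitney on change rejects |
|---|---|---|
| 0 and 1 | about 55-60% | about 81-86% |
| −0.5 and +0.5 | about 2-5% | about 78-87% |

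The arm difference is the same in both rows. The Friedman rate moves only with the average change over everybody.

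**6. How often the branch is reached.** Friedman's test comes only after a transformation has also failed. The article does not say whether normality is tested on arm-by-time cells, change scores or residuals. Simulated normal positive data were used (18 per arm, correlation 0.5; mean 300 with SD 30, and mean 8 with SD 2.3; all assumed), with the fallback taken only if both log and square root also fail:

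- Four separate arm-by-time cells, any failure decisive: 13-14% of outcomes.
- One test on arm-centred change scores: 2.5-4%.

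The first-step failure rate for four independent cells, 1 − 0.95⁴ = 18.5%, is the rate of entering the transformation step, not of reaching Friedman's test.

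**The case against.** The strongest reply is that the defect is conditional. The planned ANOVA is sound for the main question, Friedman's test comes third in a chain, and an outcome must fail twice to get there. This stands and limits the point to individual outcomes. It does not remove it, because the rule is explicit and nothing else in the section supplies an arm comparison on that branch. Since the article names a specific test, this is a wrong choice rather than a detail left to a fuller plan.

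Three stronger readings are tempting and are not supported.

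- A reader might infer that the log and square-root step is unusable for the primary outcome because mismatch negativity is a negative-going potential. The article never says whether amplitudes are kept signed or taken as magnitudes. Its single expectation, that evoked-potential amplitude increases, fits magnitudes at least as well. The step is also defined for latencies, positive P3 amplitudes and task times. What remains is that no sign handling is stated.
- A reader might take the 18.5% first-failure rate as the frequency of the problem. It ignores the transformation step and assumes four-cell testing. For truly non-normal outcomes the rate would be higher, by an amount the article gives no means of estimating.
- A reader might conclude that Friedman's test will miss a real arm difference. The near-zero rejection with −0.5 and +0.5 SD needs one trained arm to worsen, contrary to the article's expectation. In the 0 and 1 SD case it rejects in over half of trials. The fair statement is that it answers a different question, whichever way the result falls.

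**Conclusion.** The point holds, per outcome. Where non-normality persists after transformation, the named test cannot compare the arms, and the comparison on which the trial is sized goes untested. This follows from the structure of the test and needs no assumption about the data.

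The size does rest on assumptions. With equal gains of 0.8 SD of change and 18 per arm, about 97% of trials would give a significant result with no difference between methods. The branch would be reached in roughly 3-14% of truly normal positive outcomes, depending on a testing scheme that the article does not state. Outcomes analysed by the ANOVA are not affected, and the sample size calculation is not in question. The sentence should be corrected before analysis, since following it as written gives the wrong analysis. The sign question for mismatch negativity is minor and separate.

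**What to change.** Replace the Friedman sentence with wording such as:

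> Normality is judged on model residuals. If it is clearly violated and not corrected by transformation, the arms are compared by a Wilcoxon-Mann-Whitney test on post-minus-pre change, or by a permutation test of the group by time interaction.

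One of the two should be named in advance. Both keep the planned contrast and need no new model. At the planned effect the rank test on change has power of about 78-81% at 17 per arm and 86-87% at 20 per arm with normal changes. With heavy-tailed changes (t on 3 df) the figures are about 95% and 97%. It rejects in about 4-5% of trials when the arms gain equally.

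As a minor addition, limit log and square root to outcomes that are positive by definition, and state whether mismatch negativity amplitudes are analysed signed or as magnitudes. These transformations do not exist for negative values.

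The cost is one or two sentences of analysis text, with no change to recruitment, assessments or sample size.

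### Single-step Bonferroni for the post-hoc t-tests is valid but needlessly conservative; Holm's step-down on the same tests gives the same familywise control and never rejects less

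*Protocol article*

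**What the plan says.** The Expected outcomes & analysis section of the protocol article sets out the main model: "A 2-way analysis of variance (ANOVA) with repeated measures will be done considering the following factors". The factors are time (before and after training) and training group. The section plans pre/post comparisons for each method and, as its main purpose, a comparison of the game-based with the non-game-based group. It also wants to "determine if some activity yielded to a more significant difference in the overall performance".

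For follow-up comparisons it says: "Bonferroni post-hoc test will be conducted, using multiple t-tests times p-values (to avoid increase in alpha error"). The next sentence sets the level: "Analysis software to be used is Minitab with a level of significance of 0.05". No step-down method is named and the number of post-hoc tests is not given.

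The section on sample size and eligibility bases the calculation on the interaction, not on the post-hoc tests: "Sample size was calculated determining F-tests family for ANOVA repeated measures between and within interactions". Its inputs are f = 0.25, a 5% level and 80% power for two arms, each measured twice. The result is 34 in total. Forty are to be enrolled, 20 per group, allowing for about 10% loss.

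**The concern.** The wording "using multiple t-tests times p-values" is garbled, but its natural meaning is single-step Bonferroni: each p-value times the number of tests m. The article has made this choice itself and has not left it to another document.

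Single-step Bonferroni holds every test to the threshold 0.05/m, even after other tests in the family have been rejected. Holm relaxes the threshold after each rejection, with no loss of familywise control and no added assumption. The article's stated reason for adjusting, to keep the type I error from growing, is met equally well by either method.

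What is at stake is limited to the follow-up tests. With 34 to 40 people and a sample size that reserves nothing for these tests, some real differences would go undeclared that the same data could support at the same error rate.

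**Working it through.** **1. The article's own figure.** Inputs from the sample-size section: f = 0.25, alpha 0.05, power 0.80, two groups, two measurements, within-between interaction. The correlation between the repeated measures is not given; 0.5 is assumed.

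- Noncentrality: lambda = f² × N × 2 / (1 − rho), with 1 and N − 2 degrees of freedom.
- N = 34: lambda = 0.0625 × 34 × 2 / 0.5 = 8.5, power 0.807. N = 32 gives 0.781, so 34 is the smallest even total that reaches 0.80. The stated 34 reproduces.
- N = 40: lambda = 10, power 0.869.
- Other correlations give N = 66 (rho 0), 46 (rho 0.3) and 22 (rho 0.7), so 0.5 is the only value tried that returns 34.

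**2. The same effect as a difference in change.** For a two-sample t-test on change scores, lambda = d² × N / 4. Hence d² = 8.5 × 4 / 34 = 1.0, so the planning effect is 1.0 SD of change.

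**3. The two procedures.** Order the p-values p(1) ≤ … ≤ p(m).

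- Bonferroni: reject test i if m × p(i) ≤ 0.05.
- Holm: the adjusted value for p(i) is the maximum over j ≤ i of (m − j + 1) × p(j); reject if it is ≤ 0.05.

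Each Holm multiplier is at most m, so Holm's adjusted p-value never exceeds Bonferroni's. Holm therefore rejects every test that Bonferroni rejects.

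**4. Size of the gain with four tests (assumed).** Analysed n: 40 × 0.9 = 36, or 18 per arm. True difference 1.0 SD of change, so the noncentrality of t is √(18/2) = 3 on 34 degrees of freedom. At level 0.05/4 = 0.0125 the exact power is 0.642, which is the Bonferroni figure however many effects are real. Holm's figures come from simulation with correlation 0.3 or 0.5 between tests:

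| Real effects out of 4 | Bonferroni, power per real effect | Holm, power per real effect |
|---|---|---|
| 1 | 0.64 | 0.64-0.65 |
| 2 | 0.64 | 0.67 |
| 3 | 0.64 | 0.70 |
| 4 | 0.64 | 0.74-0.75 |

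If all four are real, the chance of declaring all four is 0.26-0.33 with Bonferroni and 0.52-0.57 with Holm. In no replicate did Bonferroni reject a test that Holm did not. Holm's simulated familywise error stayed below 0.05 in these settings.

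**5. Other family sizes (also assumed).** Independent tests, every effect real, power per effect, Bonferroni → Holm:

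| Tests | N = 34 | N = 40 |
|---|---|---|
| 2 | 0.71 → 0.78 | 0.79 → 0.85 |
| 4 | 0.61 → 0.73 | 0.70 → 0.82 |
| 6 | 0.55 → 0.68 | 0.65 → 0.79 |
| 8 | 0.50 → 0.63 | 0.61 → 0.76 |

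With only one real effect the gain is about 0.2 points or less.

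**6. A family drawn from the two-by-two design (assumed).** Take four simple effects: pre/post in each arm, and arm versus arm at each time. For game versus non-game after training, power goes from 0.61 to 0.65 at N = 34 with no gain in the control arm, and from 0.60 to 0.67 with a control gain of 0.5 SD. At N = 40 the figures are 0.70 to 0.74 and 0.70 to 0.77.

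**The case against.** The strongest reply is that nothing here is wrong. Bonferroni is a standard, valid adjustment; the article gives a proper reason for it and does not contradict itself. The test that matters most, the group-by-time interaction, has one degree of freedom and needs no post-hoc adjustment. The gain from Holm also depends on another test in the family being rejected first, so with one real effect it is close to nil. All of this stands, and it sets the weight of the point. It does not rescue the choice, because Bonferroni has no offsetting gain in error control.

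Two stronger readings are tempting.

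- A reader might infer that the post-hoc family is itself bloated: all six pairs of the four group-by-time cells, including pairs that cross arm and time and a baseline comparison of randomised arms. The article lists no pairs, so this cannot be charged against it. Narrowing the family to between-group contrasts of change would also remove the pre/post comparisons within each method that the article plans.
- A reader might take the full fall in power from an unadjusted test to a Bonferroni-adjusted one as the loss. Most of that fall is the price of any familywise control. The relevant comparison is Bonferroni with Holm.

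Nor does the article say that the post-hoc tests are one per sound feature. Its remark about activities only hints at that, so the four-test case above is an illustration.

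**Conclusion.** The point holds as a matter of efficiency. The article fixes a procedure that another procedure dominates on the same tests, at the same familywise level of 0.05 and under the same assumptions. Across the settings tried (two to eight tests, 34 to 40 people) the gain in power per real effect runs from about 0 to 15 points. It is near zero with one real effect, 2-3 points with two of four, and about 10 points with four of four at 18 per arm. These figures rest on assumptions the article does not settle: the number of tests, the correlation between tests, the pre/post correlation of 0.5, and true effects of 1.0 SD of change. That Holm never rejects less depends on none of them. The sized interaction test keeps its power of 0.807 at N = 34 or 0.869 at N = 40. The change is worth making but optional.

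**What to change.** In Expected outcomes & analysis, replace the phrase about multiplying t-test p-values with Holm-adjusted p-values: the smallest p times m, the next times m − 1, and so on, with each adjusted value no smaller than the one before it. Apply this to whatever family of post-hoc t-tests the trial runs, keeping the planned pre/post and between-group contrasts.

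The cost is one sentence. The same t-tests are run, no more data are needed and the familywise error stays at 0.05. The one small drawback is that simultaneous confidence intervals matching Holm are less simple than Bonferroni intervals. The change should be made before outcome data are seen, since a later switch could look driven by the results.

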## Discussion

International guidelines suggest auditory training as an important part of the aural rehabilitation process supplementing hearing loss management best practices [8,39]. Several reports in the last decades have shown that AT can benefit both hearing impairment and normal hearing population to improve sensory and perceptual auditory responses. As mentioned in State of Art, there has also been some research in the last decade about computer-based and game-based AT. Some of these have developed their own software and some others have used commercial programs. Most research has been focused on demonstrating improvement in cognitive-auditory processing assessments and tasks, mainly oriented in speech recognition and dichotic-based training.

Very little was found in the literature about validation criteria and usability evaluation for digital tools such as games, apps, or web software that in fact contribute to the overall benefit of the AT and that answer the question of how is game experience and training engagement related to improvement in AT performance? Some interesting findings have been presented by Whitton [21] that tried to develop a new proposal of AT tasks, although no validation of the methodology in terms of the framework was done.

Another interesting finding was done by Larrea-Mancera et al. [15] in the gamified AT approach integrating perceptual learning and video-game play for speech competition with a mixed training with three activity modules. Designing the training based on game experience presented in an obstacle avoiding or “runner” format game, based on motivation for broad improvements in visual and cognitive processing skills enhancement by gamification.

Lastly and following this line for auditory computer-based training validation, Tuz [16] explored the importance of the user program evaluation through usability questionnaires and established a consistent antecedent for subjective validation of the methodology. Although results of the AT performance were not published yet, it suggested a starting point for game-based auditory training user evaluation.

All these studies still did not explore the performance of training directly on discrimination thresholds estimation through audio neurological procedures to ensure a change not only on brain plasticity but in auditory processing, frequency response and neural timing.

This study tries to find a relationship experience-performance in AT, specifically, addressing game elements and engagement in auditory processing improvement.

As part of some issues considered during the performing of the study, limitations found are the following:

Restriction by installations and equipment to be used calibration and justification of study setting and materials will be included as part of the final publications.Study design depends on participants constant and correct usage of auditory training methodology. Since daily monitoring of 50 participants is not possible, monitoring will be done every week.Sample size is above as the calculated sample size considering participants withdrawal of 10%, although withdrawal rate could be different.

With scientific dissemination purposes, once analysis is concluded research it is intended to publish results as original research paper, analyzing auditory processing discrimination results through AT performance and electrophysiological measurements. Research would be published in journals related to auditory health, auditory neuroscience, or physiological acoustics approximately by the end of 2025. With transparency purposes participants’ measurements data will also be intended to be published by the same date in database repository, so it can be available for further research.

Once evaluated the generality of the study, amendments considered for future research are the following:

To have more measurements in time and monitor participants training continuity and to have a follow up with one last measurement after some specific time after training.To meet one more inclusion criterion based on auditory processing tests to determine if there exists any irregularity among participants.To have specialized medical equipment to obtain other participants audiological assessments.To apply longer AT sessions and during more time to measure improvement to long-time exposure effect.To develop a higher number of game-based audiologic tasks and levels to have a broader evaluation.To change recruitment target to hearing-loss population, so once tool and methodology are validated new improvements can be measured in this population.

With this research it is expected that auditory processing improvement can be addressed by the efficient use of engaging computerized resources such as game-based training tools, permitting further works that may benefit and contribute to hearing impairment and auditory disorder populations potentially in auditory discrimination, sound localization and lateralization, auditory pattern recognition, and temporal processing.
